### Study-specific visits and procedures

The schedule for all study procedures for all evaluations is shown in Fig. 2. For each procedure, individuals are to be assessed by the same investigator or site personnel whenever possible. The timing of each visit is relative to randomization (day 0). Baseline measures (visit 1 and visit 2) include medical history (demographic characteristics, medical and treatment history, complicating disease, signs and symptoms, concomitant medications), clinical blood pressure, 24-h ambulatory blood pressure, vasoactive factors, four hormones related to hypertension, inflammatory mediators, TCM syndrome score, and SF-36 score. All baseline measurements will be repeated at visit 4 for all participants. AEs and outcome measurements will be recorded from visit 3 to visit 4.

### Randomization and blinding

Participants are randomized in a 1:1 ratio using a computer-generated, site-stratified, block randomization schedule. The study capsules will be labeled with sequential randomization numbers and each patient will be assigned the lowest number available at each participating center. All patients, care providers, and attending physicians will be blinded to treatment assignment until the study is completed. Duplicated blinding codes will be given to the main research institution and the manufacturer; the blinding codes cannot be revealed during the trial.

### Data entry and quality control of data

CRFs are being used for data entry and data from all participating centers will be imported into the clinical data management system (http://www.xyedc.com/). To maintain the quality of data, we will adopt valid measures to ensure information accuracy, integrity, and authenticity. First, computer logic checks will be run to identify items such as inconsistent data, missing data, and questionable values. After that, the supervisor will perform source data verification to check the consistency of the original data. Queries may be issued by the supervisor, which will be answered by the site investigators. Second, manual checks will identify more complicated and less common errors. Third, the supervisor will conduct site visits to compare the electronic database with the source documents. Identified errors will be resolved to ensure data quality. Fourth, the Data Coordination Center will be in charge of data validation.

### Sample size calculation

The sample size was calculated based on the expected reduction in hypertension. A meta-analysis has showed that SXC combined with antihypertensive drugs is more effective in lowering both the systolic blood pressure (SBP) (MD: -6.17 [− 7.86, − 4.49]; *P* < 0.01) and diastolic blood pressure (DBP) (MD: -7.24 [− 8.62, − 5.85]; P < 0.01) compared with that by antihypertensive drugs alone [14]. Furthermore, a small sample clinical trial has shown that SXC is effective in lowering the 24-h SBP by approximately 14 mmHg (mean SBP of 136.3–122.3 mmHg) after a four-week treatment period; however, the quality of the trial was relatively low [19]. According to these reports [14, 15, 19], it is assumed that the 24-h average SBP can be decreased by approximately 12 mmHg in the SXC test group and 5 mmHg in the placebo group. Assuming that the bound of value = 5 and standard deviation (SD) = 7 for the test and placebo groups, combined variance σ^2^ = 49, type I error rate (α) = 0.05, and a power of 90% (type II error rate (β) = 0.1), the sample size for one arm needed to be 258, resulting in *n* = 2 × 258 = 516 (bilateral test level α = 0.05, test efficacy β = 90%). Considering a dropout rate of 10%, a total of 570 patients needed to be allocated to attain the required number of patients for the efficacy analysis.$$ {\displaystyle \begin{array}{l}{n}_c=\frac{\left(1+\frac{1}{k}\right)\kern0.28em {\left({\mu}_{1-a}+{\mu}_{1-\beta}\right)}^2\kern0.28em {\sigma}^2}{{\left[\left({x}_T-{x}_c\right)-\Delta \right]}^2}\\ {}{n}_t={kn}_c\end{array}} $$

### Statistical analysis

The data from all participating centers will be combined for statistical analysis of primary and secondary endpoints, as well as AEs.

The analysis will be performed at the Clinical Pharmacology Research Institute, Xiyuan Hospital, China Academy of Chinese Medical Sciences. Continuous variables will be presented as the mean ± SD. The comparability of characteristics between the two study groups will be assessed using a two-sample Student’s *t-*test for continuous variables and the χ^2^ test or Wilcoxon test, when appropriate, for categorical variables. The Wilcoxon paired signed-rank test will be used for within-group comparisons.

For all analyses, *P* < 0.05 will be considered statistically significant, and all tests will be two-tailed. All analyses will be conducted using SAS software version 9.2 (SAS Institute, Cary, NC, USA).

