### Randomization and treatment assignment

Patients are randomized in a 1:1 ratio through a centrally controlled, computer-generated, site-stratified, block randomization schedule. The study capsules are labeled with serial numbers; each patient will be assigned the lowest number available at each participating center. All patients, care providers, attending physicians, laboratory staff, and biostatisticians are blinded to treatment assignment as long as the database is locked. Randomization started on May 2017. The enrolment of 570 patients is expected to be completed in August 2019.

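### Site-stratified randomization and a measured baseline 24-h pressure go unused: no test the article names, nor its sample-size formula, adjusts for site or baseline, so precision available at negligible cost is lost

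*Protocol article*

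**What the plan says.** **Design.** The section Randomization and treatment assignment states: "Patients are randomized in a 1:1 ratio through a centrally controlled, computer-generated, site-stratified, block randomization schedule". The section Randomization and blinding repeats the site stratification, and Study design gives seven centres.

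**Measurements.** Outcomes and measures names 24-h ambulatory systolic and diastolic pressure as primary. Study-specific visits and procedures lists 24-h ambulatory pressure among the baseline items (the sentence begins "Baseline measures (visit 1 and visit 2) include medical history") and adds: "All baseline measurements will be repeated at visit 4 for all participants".

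**Analysis.** Statistical analysis opens with "The data from all participating centers will be combined for statistical analysis of primary and secondary endpoints, as well as AEs". It then names a two-sample t-test for continuous variables and chi-square or Wilcoxon tests for categorical ones, in a sentence about whether the groups are comparable, and a signed-rank test within groups. No model with a site or baseline term is named.

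**Sample size.** The calculation assumes that 24-h SBP is "decreased by approximately 12 mmHg in the SXC test group and 5 mmHg in the placebo group", with a bound of 5 mmHg, an SD of 7 and a variance of 49, "bilateral test level α = 0.05" and "a power of 90% (type II error rate (β) = 0.1". The result is 258 per arm. The variance carries no reduction for baseline or site.

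**The concern.** Two features of the design could sharpen the treatment comparison, and nothing in the analysis text uses them.

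- **Site.** When randomization is balanced within sites, variation between sites largely cancels out of the treatment difference. A two-sample test still counts that variation in its standard error. The standard error is then too large and the test conservative.
- **Baseline.** The pre-randomization 24-h pressure can be expected to predict the visit-4 value. An analysis without it leaves explainable variance, and any chance baseline imbalance, in the estimate. A change score uses baseline, but with a fixed coefficient of one; ANCOVA estimates the coefficient and is at least as precise in large samples.

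At stake is precision: a wider confidence interval, and less power against the 5 mmHg bound, than the same patients could provide.

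**Working it through.** **Inputs from the article (Sample size calculation).** Expected falls 12 and 5 mmHg, difference 7; bound 5; SD 7; "type I error rate (α) = 0.05", two-sided; power 90%; 1:1 allocation.

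**Inputs assumed.** The article gives neither the baseline-to-visit-4 correlation r, taken as 0.3 to 0.8, nor the share s of outcome variance lying between sites, taken as 2% to 10%. It also does not say whether SD 7 describes the change or the level, so both readings are shown.

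**Step 1: reproduce the plan's figure.** Net difference = 7 − 5 = 2 mmHg.

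n per arm = 2 × 49 × (1.960 + 1.282)² / 2² = 257.4, rounded up to 258.

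This matches the article. A one-sided 0.05 would give 210, which does not. At 258 per arm the standard error is 7 × √(2/258) = 0.616 mmHg, 2/0.616 = 3.245, and power = Φ(3.245 − 1.960) = 90.1%. The plan is therefore sized for an unadjusted comparison.

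**Step 2: adjust for baseline.** ANCOVA multiplies the planning variance of 49 by

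- (1 + r)/2 if SD 7 is the SD of change, because the change has variance 2σ²(1 − r) and the ANCOVA residual σ²(1 − r²);
- 1 − r² if SD 7 is the SD of the level.

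| r | Factor, SD of change | n per arm for 90% | Power at 258 | Factor, SD of level | n per arm for 90% | Power at 258 |
|---|---|---|---|---|---|---|
| 0.3 | 0.65 | 168 | 98.1% | 0.91 | 235 | 92.5% |
| 0.5 | 0.75 | 194 | 96.3% | 0.75 | 194 | 96.3% |
| 0.6 | 0.80 | 206 | 95.2% | 0.64 | 165 | 98.2% |
| 0.7 | 0.85 | 219 | 94.1% | 0.51 | 132 | 99.5% |
| 0.8 | 0.90 | 232 | 92.8% | 0.36 | 93 | over 99.9% |

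The size of the gain depends on r and on the reading of SD 7. Its direction does not, since both factors are below 1 for every r strictly between 0 and 1.

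**Step 3: add site.** A site term multiplies the variance by a further (1 − s). With r = 0.5 and s = 5%, the factor is 0.75 × 0.95 = 0.7125, giving 184 per arm for 90% power, or 97.0% power at 258.

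**Step 4: error rate if site is ignored.** The true two-sided error is about 2 × [1 − Φ(1.960/√(1 − s))]:

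- s = 2%: 4.8%
- s = 5%: 4.4%
- s = 10%: 3.9%

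**Step 5: cost of adjusting.** One baseline term and six site terms use 7 of 514 degrees of freedom. The critical t moves from 1.96459 to 1.96465. Chance covariate imbalance inflates the variance by about 513/506 = 1.014, or 1.4%, most of it (about 1%) from the six site terms. If site explained nothing, ANCOVA would still break even at 1 − r² = 506/513, that is r ≈ 0.12, on the level reading, and would gain for any r below about 0.97 on the change reading.

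**The case against.** The strongest reply is that the article names no efficacy test at all. The t-test sentence concerns comparability of the groups, the signed-rank test is within-group, and a condensed article may leave the primary model to an analysis plan that is not shown. This stands in part: one cannot say that the sponsor has committed to an unadjusted t-test for 24-h pressure. It remains true that every between-group test named, and the sample-size formula, are unadjusted. An analysis plan written to match would be unadjusted too.

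Second, pooling the centres does not rule out a site term, because an ANCOVA with site is also fitted to pooled data. That is right. The sentence on combining data shows only that no site term is mentioned.

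Third, the practical gain may be small. The Statistical analysis section mentions no test against the 5 mmHg bound. Against zero, the planned 7 mmHg difference is 7/0.616, about 11 standard errors, so power is essentially 100% either way. This stands too. The benefit is then a narrower interval: at a variance factor of 0.80, the 95% half-width falls from 1.96 × 0.616 = 1.21 mmHg to 1.21 × √0.80 = 1.08 mmHg.

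A reader might infer two further defects that the article does not support.

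- **A noisy baseline taken before the run-in.** The text lists visits 1 and 2 together as baseline. The schedule showing which item falls at which visit is in a figure not available here, and nothing says that a pre-run-in recording would be the reference value.
- **Power of only 83% for a comparison of raw visit-4 values.** This needs r = 0.6, SD 7 to be the SD of change (so that the SD of the level is 7/√0.8 = 7.83), and a raw-value analysis. The article states none of these, and it plans on the fall in pressure. If SD 7 is the SD of the level, the raw comparison has the planned 90%.

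**Conclusion.** The point holds as a recommendation on efficiency. The article describes a site-stratified design with a baseline measurement of the primary outcome, and names no analysis that uses either. At the planned 258 per arm, ANCOVA would lift power against the 5 mmHg bound from 90% to about 93–98% (SD 7 as change) or to about 92.5% to over 99.9% (SD 7 as level). These ranges are for baseline adjustment alone and rest on the assumed correlations of 0.3 to 0.8; a site effect would add to them.

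It would be wrong to conclude that the trial is biased, invalid or undersized on this account. Randomization protects the unadjusted comparison. Ignoring site makes it mildly conservative (about 4.8% to 3.9% instead of 5%, if site explains 2% to 10% of the variance), and the stated sample size reaches its 90% without adjustment. The change is worth making because the gain is nearly free. It also settles in advance whether level, change or an adjusted value is compared.

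**What to change.** Name the primary analysis as ANCOVA of visit-4 24-h mean SBP on treatment, the last 24-h mean SBP recorded before randomization, and site (seven levels). Report the adjusted treatment difference with its 95% confidence interval. Use the same model for DBP, daytime and night-time pressure, each with its own baseline value. Compare the hypertension control rate with a test stratified by site, such as Cochran–Mantel–Haenszel.

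State whether SD 7 refers to change or to level. The enrolment target can stay at 570, since the unadjusted calculation is conservative for this model.

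The cost is a wording change in the protocol or analysis plan. No extra patients, visits or measurements are needed, and the statistical price is the 7 degrees of freedom and roughly 1% of variance shown above. The Trial status section reports that no analysis had been done, so the model could still be prespecified at that stage.

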## Discussion

In this trial, we will assess the efficacy and safety of SXC in treating patients with low-to-medium risk hypertension. The present study is designed as a multicenter, double-blind, randomized, placebo-controlled, parallel-group superiority trial that will provide high-powered evidence regarding the efficacy and safety of SXC in treating patients with low-to-medium risk hypertension.

A previous study showed that pine needle extract has pharmacological properties that modulate hippocampal excitotoxicity-derived memory impairment under severe stress conditions [20]. In salt-sensitive hypertension, puerarin improves vascular insulin action with beneficial cardiovascular effects [21]. In addition, through the regulation of the apelin/APJ system, puerarin exerts protective effects on the development of left ventricular hypertrophy by renal hypertension [22]. The large- and small-molecule fractions of high temperature-extracted pearl extract exert a conspicuous sedative effect. The high-temperature-derived extract has been found to improve the vitality and anti-hypoxia abilities of mice. Low-temperature-extracted pearl powder increases the level of superoxide dismutase and decreases the level of malondialdehyde in the blood serum [23]. Previous studies have shown that SXC has a potential blood pressure-lowering effect, leading to the improvement of plasma levels of endothelin and nitric oxide, thereby regulating the renin-angiotensin system [24, 25]. These findings and observations provide an impetus for large-sample controlled trials to investigate the efficacy of SXC in the treatment of patients with low-to-medium risk hypertension.

For patients with low-to-medium risk hypertension, the current domestic and foreign guidelines generally recommend lifestyle improvement and monitoring of blood pressure and other risk factors 1–3 months before deciding whether to carry out drug treatment. Therefore, 10 weeks of follow-up monitoring and placebo therapy will not cause irreversible damage to the individuals [19].

There are certain limitations to this study. First, because the study is being performed in Beijing, China, it is uncertain whether the relative effects of the trial drugs would be similar in other ethnic groups. Second, the follow-up period is relatively short.

Nevertheless, this trial aims to evaluate the efficacy and safety of SXC for the treatment of patients with low-to-medium risk hypertension.

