## Methods/design

### Study objectives

This study aims to determine the efficacy of SXC in patients with low-to-medium risk hypertension.

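### The claim of high-powered evidence on safety has no basis in a trial sized only for 24-h SBP, and it fails for uncommon adverse events

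*Protocol article*

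**What the plan says.** The Discussion states that the trial "will provide high-powered evidence regarding the efficacy and safety of SXC in treating patients with low-to-medium risk hypertension". Efficacy and safety share one claim of power.

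The rest of the article supports that claim for efficacy only:

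- Study objectives: "This study aims to determine the efficacy of SXC in patients with low-to-medium risk hypertension". Safety is not named there.
- Sample size calculation: "The sample size was calculated based on the expected reduction in hypertension". The assumption is that "the 24-h average SBP can be decreased by approximately 12 mmHg in the SXC test group and 5 mmHg in the placebo group", with "Assuming that the bound of value = 5 and standard deviation (SD) = 7 for the test and placebo groups", two-sided α of 0.05 and 90% power. This gives 258 per arm and 516 in total, raised to 570 for dropout. The section ties the 570 to the efficacy analysis.
- Statistical analysis: "The data from all participating centers will be combined for statistical analysis of primary and secondary endpoints, as well as AEs". Later in the same section: "For all analyses, *P* < 0.05 will be considered statistically significant, and all tests will be two-tailed".

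The article gives no expected AE rate, no excess risk to be ruled out and no precision target for any safety outcome. Outcomes and measures lists blood, urine, liver and renal tests and electrocardiograms. Adverse events provides for monthly enquiry and a data safety monitoring board.

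**The concern.** Power belongs to a stated comparison, effect size and sample size. A trial with 90% power for a difference in mean blood pressure may have very little power for a difference in the incidence of an uncommon harm. The article claims the property for safety without establishing it.

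The results will inform the use of SXC alone, against placebo, in low-to-medium risk patients. If AEs are compared under the general P < 0.05 criterion and the difference is not significant, a reader who has been told that the safety evidence is high-powered may take the result as reassurance. For uncommon events the data could not give that reassurance.

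**Working it through.** **1. Reproduce the planned size.** Inputs from Sample size calculation: reductions of 12 and 5 mmHg, bound 5, SD 7 (variance 49), two-sided α = 0.05, power 90%, 1:1 allocation.

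n per arm = 2 × (1.960 + 1.282)² × 49 / [(12 − 5) − 5]² = 2 × 10.507 × 49 / 4 = 257.4, rounded up to 258.

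The total is 516. For 10% dropout, 516 / 0.90 gives 574 and 516 × 1.10 gives 568. The planned 570, or 285 per arm, lies between them. The figures therefore reproduce, and every input concerns 24-h SBP.

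**2. Power for a doubling of AE incidence.** The article gives no AE rates, so the placebo rates below are assumptions. The test is the two-sided uncorrected chi-square test at 0.05. Power was found by summing the joint binomial probabilities of all tables that reject. The figure of 285 per arm counts everyone randomized; 258 counts the number left after the planned dropout.

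| Placebo vs SXC | Power, 285 per arm | Power, 258 per arm |
|---|---|---|
| 1% vs 2% | 15.0% | 13.8% |
| 2% vs 4% | 29.0% | 26.6% |
| 3% vs 6% | 41.0% | 37.5% |
| 4% vs 8% | 53.0% | 48.5% |
| 5% vs 10% | 63.2% | 58.7% |
| 8% vs 16% | 84.5% | 80.8% |
| 10% vs 20% | 92.4% | 89.7% |

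Hand check of 2% vs 4% at 285 per arm by the normal approximation:

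- Standard error under no difference: √(2 × 0.03 × 0.97 / 285) = 0.01429.
- Standard error under the alternative: √[(0.02 × 0.98 + 0.04 × 0.96) / 285] = 0.01427.
- Power = Φ[(0.02 − 1.96 × 0.01429) / 0.01427] = Φ(−0.56) = 0.29, in agreement with the table.

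By the same approximation, power reaches 50% at a placebo rate of about 3.8% (4.2% with 258 per arm), 80% at about 7.3% (8.0%) and 90% at about 9.4% (10.3%). For 80% power to detect a doubling, the size needed per arm is 2,319 from 1%, 1,141 from 2%, 435 from 5% and 199 from 10%.

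**3. What a non-significant result would leave open.** Suppose 6/285 events on placebo and 13/285 on SXC. The difference is 7/285 = 2.5 percentage points. The pooled rate is 19/570 = 0.0333, so z = 0.02456 / √(2 × 0.0333 × 0.9667 / 285) = 1.63 and P = 0.10. The Newcombe 95% interval for the risk difference runs from −0.6 to +5.7 points. This comparison would be called not significant, yet the data allow an excess of more than 5 points.

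**4. No events at all.** With zero events among 285 SXC patients, the one-sided 95% upper bound on the true rate is 1 − 0.05^(1/285) = 1.05%. With 258 patients it is 1.15%.

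**The case against.** The case on the other side has four parts.

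- **The power is not always low.** This stands. A doubling from 8% is detected with about 84% (81%) power and one from 10% with about 92% (90%). Any AE may well be that common. A reader might infer that a doubling of AEs would usually be missed in this trial; the document does not support that, because it gives no AE rate and the statement is true only below a placebo rate of about 4%.
- **No safety decision rule is stated.** This also stands. A reader might infer from the blanket P < 0.05 that a non-significant AE comparison will count as evidence of safety. The Statistical analysis section says only what will be called significant. It attaches no meaning to a non-significant result and names no test for AEs.
- **Detail on AE analysis may sit in the full protocol or the SAP.** This is right, and the lack of AE tables or margins in a journal article is not the fault raised here. It does not rescue the Discussion sentence: a later analysis plan cannot supply power for safety when the sample size was fixed on blood pressure.
- **Safety does not rest on a P value alone.** Monthly enquiry, periodic tests and the monitoring board are real protections, and the Discussion admits that follow-up is short. They help to collect and watch for harms, but they do not add power to a comparison between arms.

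**Conclusion.** The point holds in a limited form. The Discussion claims a power property for safety that the document never establishes. The claim is untrue for uncommon harms: under assumed placebo rates of 1% to 3%, power to detect a doubling is about 14% to 41% across the two sample sizes. It may be true for common outcomes, with about 81% or more from a placebo rate of 8% upward.

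These sizes rest on assumed placebo rates, on a doubling as the effect of interest, and on an uncorrected chi-square test. Fisher's exact test would give less power (21% for 2% vs 4% at 285 per arm).

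The severity is minor. The design, the sample size and the primary analysis are unaffected; what changes is the strength of the safety conclusion the trial can support.

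**What to change.** 1. In the Discussion, limit the high-powered claim to efficacy on 24-h SBP. Add that the trial is not powered to exclude differences in uncommon AEs.
2. In Statistical analysis, state that AE incidence and the proportions with out-of-range safety results will be reported as risk differences (SXC minus placebo) with two-sided 95% confidence intervals. State that safety conclusions will rest on those intervals, and that P > 0.05 will not be taken as evidence of safety.

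The cost is two changes of wording and one extra table from data already being collected, with no more patients. The Trial status section reports enrolment still open and no analysis done, so at that stage the change could be made before unblinding. The drawback for the sponsor is a more modest safety claim.
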